### Safety assessment

All AEs according to the Common Terminology Criteria for Adverse Events (CTCAE) will be collected and documented, regardless of severity, seriousness, or relationship to the study drug. We will summarize all AEs, include AE frequency and percentage, and 95% CIs and compare the occurrence rate of AEs in relationship to the study drug and the severity of the two arms using the chi-square test or Fisher’s exact test.

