### Design

This is a prospective, open-label, randomized controlled, multicenter clinical study with two arms. Eligible patients are first screened by safety laboratory testing. Patients with diagnosed mild/general COVID-19 infection are randomized to the following two arms at a 1:1 ratio:
Arm 1 (control arm): lopinavir/ritonavir treatment for diagnosed mild/general COVID-19 infection uses lopinavir 800 mg/day and ritonavir 200 mg/day for no more than 10 daysArm 2 (investigation arm): chloroquine phosphate treatment using chloroquine phosphate 1000 mg/day, equivalent to chloroquine 600 mg/day for no more than 10 days

The CRF is shown in Fig. 1. The schedule of treatment visits and data collection (also known as the CRF) is shown in Table 1.

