### Definitions

#### The clinical recovery time and adverse events

We define the clinical recovery time as the time (in hours, no more than 28 days) from the start of study drug intervention to normalization of body temperature, respiratory symptoms (cough, nasal stuffiness, nasal discharge, etc.), respiratory frequency, and blood-oxygen saturation. Specifically, also meeting the following criteria at the same time:
① No fever: axillary body temperature ≤ 37.2 °C② Relief of respiratory symptoms (72 consecutive hours)③ Respiration rate ≤ 24/min (resting state)④ Fingertip blood oxygen > 94%

Adverse events (AEs) refer to adverse medical events that occur after a patient or clinical trial participant receives a drug, but they are not necessarily causally related to treatment.

Serious adverse events (SAEs) refer to events that require hospitalization, prolonged hospital stay, disability, affect working ability, are life-threatening or fatal, cause congenital malformation and other events that occur during the clinical trial.

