#### Analysis of secondary outcomes

The analysis of secondary outcomes will be described as explorative outcomes. The rate of treatment success after the completion of therapy and follow-up among the two groups will be compared using the chi-square test or Fisher’s exact test. The time of treatment success after no more than 28 days, the time to normal temperature (calculated from the onset of illness) during the completion of therapy and follow-up will be calculated in each group and compared using the log-rank test.

The rate of SAEs during the completion of therapy and follow-up will be compared among the two groups using the chi-square test or Fisher’s exact test.

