### Limitations

Randomized controlled studies still have some design limitations. First, the sample size we use is relatively small and the 28-day treatment period is short. Therefore, we will not be able to estimate possible relapses of pneumonia after long-term treatment. Second, the pathophysiology of novel coronavirus pneumonia has not been elucidated. As only clinician assessment is used (including lung computed tomography (CT) results and count of viral load), there is no objective indicator to judge the effect of treatment on COVID-19 infection. Finally, the follow-up period in this study was relatively short. In light of these limitations, we will develop a more reasonable treatment cycle and follow-up period to explore the efficacy of chloroquine in patients with COVID-19.

We also know that there will be many biases in the open trial, and we have taken a number of measures to control the possible bias in the trial, as follows:

(1) Strict exclusion criteria are formulated to effectively control other confounding factors that may affect the efficacy; (2) the trial uses random grouping to ensure that the two groups of patients are comparable; (3) before the patient signs the informed consent form, the researchers and the patients make full communication to ensure that the patients understand the entire trial content, and try to eliminate the impact of the patient’s psychological state on the trial effect; (4) the main and secondary indicators for evaluating the efficacy are objective indicators to avoid the influence of subjective factors; (5) before the start of the trial, the researchers will conduct unified system training to ensure the uniformity and correctness of data collection and index evaluation.

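### The protocol tests adverse events between arms by relationship to study drug and by severity, but names no clear test of any adverse event regardless of relationship, although the trial is open-label

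*Protocol article*

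**What the plan says.** All references are to the protocol article.

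- **Collection (Safety assessment).** AEs, graded by CTCAE, "will be collected and documented, regardless of severity, seriousness, or relationship to the study drug".
- **Definition (The clinical recovery time and adverse events).** AEs follow receipt of a drug, "but they are not necessarily causally related to treatment".
- **Summary (Safety assessment).** "We will summarize all AEs, include AE frequency and percentage, and 95% CIs".
- **Named between-arm AE test (Safety assessment).** The plan is to "compare the occurrence rate of AEs in relationship to the study drug and the severity of the two arms using the chi-square test", with Fisher's exact test as the alternative.
- **Serious AEs (Analysis of secondary outcomes).** "The rate of SAEs during the completion of therapy and follow-up will be compared among the two groups using the chi-square test", again with Fisher's exact test as the alternative. Neither this sentence nor the definition of a serious AE restricts the test to drug-related events.
- **Masking (Design).** "This is a prospective, open-label, randomized controlled, multicenter clinical study with two arms".
- **Acknowledged bias (Limitations).** "We also know that there will be many biases in the open trial". Five countermeasures follow. The one about objective indicators concerns efficacy, and none describes a masked or independent assessment of causality.

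**The concern.** Randomisation protects a comparison of AEs from all causes. It does not protect a comparison of AEs that have been filtered, after randomisation, by a judgement on whether the drug caused them. In an open-label trial that judgement may be made with knowledge of the arm. Here it also concerns a different drug in each arm, so the question answered is not the same on the two sides. If a larger share of events is put down to the drug in one arm, the test can show a difference when the true incidence is equal, or miss one when it is not.

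The Discussion part of the abstract makes a finding that chloroquine is safe one of the conditions for taking it further. The AE comparison that carries a p-value should therefore rest on the count that randomisation protects. The data for that count are already collected.

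**Working it through.** The documents give no AE rates and no attribution rates, so there is no planned figure to reproduce for this test. What follows shows how sensitive the test is; it does not predict what will happen in the trial.

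**Inputs from the protocol.** 56 patients per arm (Sample size); two-sided 5% level (Efficacy outcomes, applied here to the AE test); chi-square test (Safety assessment).

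**Assumptions.** The unit is the patient with at least one AE. The true AE incidence is p1 and p2 in the two arms. A share a1 and a2 of affected patients is judged drug-related. The related-AE rates are then p1 × a1 and p2 × a2. The rejection probability comes from exact enumeration of two binomials with n = 56 each, using the uncorrected Pearson chi-square test.

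**1. Equal true incidence, p1 = p2 = 40%**

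| Attribution a1 vs a2 | Related-AE rates | False-positive rate |
|---|---|---|
| 50% vs 50% | 20% vs 20% | 5.2% |
| 55% vs 45% | 22% vs 18% | about 8.5% |
| 60% vs 40% | 24% vs 16% | 18.8% |
| 70% vs 40% | 28% vs 16% | 34.0% |

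Over a true incidence of 30% to 60%, the range is 14% to 29% at 60% vs 40% attribution, and 25% to 54% at 70% vs 40%. A gap of 10 points (50% vs 40% attributed) gives only 7% to 11%. A test of any AE stays at about 5% throughout.

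Fisher's exact test, the protocol's alternative, is more conservative but does not remove the effect. At 40% incidence it gives 2.8% with equal attribution, 12.6% at 60% vs 40% and 25.8% at 70% vs 40%.

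**2. A true excess, p1 = 50% vs p2 = 25%**

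| Count tested | Rates compared | Power |
|---|---|---|
| Any AE | 50% vs 25% | 79% |
| Related, 60% attributed in both arms | 30% vs 15% | 49% |
| Related, 50% vs 70% attributed | 25% vs 17.5% | 17% |
| Related, 40% vs 80% attributed | 20% vs 20% | 5% |

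The second row matters for reading the others. Of the fall from 79% to 17%, 30 points (79 − 49) already arise from dropping unrelated events equally in both arms. The remaining 32 points (49 − 17) come with the unequal attribution. The last row is constructed so that the two related rates coincide exactly; it marks an extreme.

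**3. What the wording covers.** The test sentence can be read as two comparisons, one by relationship and one by severity, or as related AEs classified by severity. Under the first reading the severity comparison covers all AEs and passes through no attribution filter. Under neither reading is an overall test of any AE clearly named.

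**The case against.** The case against giving this much weight is substantial.

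- **Relatedness is not the only comparison.** The same sentence compares AEs by severity, most naturally across all AEs, and serious AEs are tested without a causality restriction. This stands, and it limits the harm. The serious-AE test does not reach non-serious events, and the severity wording is ambiguous.
- **All-cause AEs are not hidden.** They are summarised with percentages and 95% confidence intervals, so a real excess would be visible. This stands. What remains is that the p-values attach to relatedness and severity, not clearly to any AE overall.
- **Who judges relatedness is not stated.** This also stands. Knowledge of the arm is an inference from the open-label design and the absence of any described masking. The full protocol, which is not shown, may say more.
- **The illustration uses large gaps.** The larger figures need attribution to differ by 20 points or more, and a small gap does little.
- **This is ordinary reporting.** Tabulating AEs by relationship and severity beside an all-AE summary is common practice. That is fair for a table. It is a weaker defence of a between-arm significance test on relatedness in an open-label trial.

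A reader might go further and infer that attribution will differ because chloroquine is the new drug and lopinavir/ritonavir the familiar one. The documents do not support that. The abstract does speak of a new treatment, but the Background presents chloroquine as an established drug, and the Discussion says the seventh edition of the national treatment plan recommends both. No direction of bias can be drawn from this.

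**Conclusion.** The point holds in a limited form. The protocol names between-arm AE tests by relationship and by severity, and no clear test of any AE regardless of relationship. With an open-label design, no described masked causality assessment and a different study drug in each arm, the relatedness test is open to distortion in either direction. The documents do not show that attribution differs, or which arm it would favour.

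The size depends wholly on assumed rates. At 56 per arm and 40% incidence in both arms, the false-positive rate rises from 5% to about 8.5% for attribution of 55% vs 45%, to 19% for 60% vs 40% and to 34% for 70% vs 40%.

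It would be too strong to say that the trial's safety conclusion rests on the attributed count, or that a real excess could disappear from the report. The severity comparison, the all-AE summary with intervals and the all-cause serious-AE test would remain. Priority is minor to moderate.

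**What to change.** In the Safety assessment section, state that the main between-arm AE comparison is the proportion of patients with at least one AE regardless of relationship, overall and by CTCAE severity, with the risk difference and its 95% confidence interval. Report AEs judged related to the study drug by arm as descriptive or supportive only, and note beside them that the trial is open-label.

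The cost is a sentence or two of text. The data are already collected, so no extra patients, visits or staff are needed. The downside is that all-cause AEs include symptoms of the disease itself, which add background noise to the comparison.

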### Data collection and management

Our study will use a paper version of the case report form (CRF) and establish a clinical research database to record all the information in the CRF. We will use the software Epidata 3.1 for double data entry and proofreading of data, as well as manual verification and system verification.

During the study, medical personnel not participating in this study will monitor this trial. Monitors will visit the database to monitor all aspects of the study including adherence to the protocol and good clinical practice, protection of participants, and data accuracy of the study.

### Supervision of the trial

The Office of the Clinical Research Center and the Medical Ethics Committee of Sun Yat-sen University form the Data and Safety Monitoring Board. Based on data review during the trial conduct, the Board may provide recommendations such as protocol amendment, continuation, or stopping of the trial. The datasets analyzed during the current study are available from the corresponding author on reasonable request.

### Confidentiality

We will collect the participants’ personal information only when necessary to evaluate efficacy, safety, and tolerability of the study drugs. Such information will be collected and processed, taking precautions for compliance with laws on privacy protection and the guarantee of confidentiality. Paper files containing participants’ data (including personally identifiable information and copies of signed consent forms) will be securely stored in a locked office on sites in locked filing cabinets. Digital files containing participants’ data will be stored in password-protected files on university-maintained servers. Access to study files will be restricted to authorized personnel only.

The items in the present study protocol comply with the Standard Protocol Items: Recommendations for Interventional Trials (SPIRIT) Checklist (see the SPIRIT Checklist and figure in Additional file).

### Clinical trial registration

The trial was registered under the registration number ChiCTR2000029741 (http://www.chictr.org.cn/showproj.aspx?proj=49263) on 11 February 2020. On 10 February, 2020, this research was approved by the Medical Ethics Committee of the Fifth Affiliated Hospital of Sun Yat-sen University, ZDWY[2020] Lunzi No. (K15–1).

## Discussion

As of 10 April 2020, the total number of COVID-19 infection diagnoses in the world was more than 1.3 million, with more than 80,000 deaths (https://www.who.int/dg/speeches/detail/the-cooperation-council-of-the-turkic-speaking-states%2D%2D-10-april-2020). There is no known curative treatment for COVID-19, neither novel treatments nor vaccines. Cao’ study observed no benefit with lopinavir/ritonavir treatment in severe COVID-19 patients [19]. Lim’s study observed that the beta-coronavirus viral load significantly decreased with no or little coronavirus titers after administering lopinavir/ritonavir [2]. Gautret’s study [20] concluded that chloroquine is significantly associated with viral-load reduction/disappearance in COVID-19 patients. In the seventh edition of the Chinese version of the COVID-19 Diagnosis and Treatment Plan (http://www.nhc.gov.cn/yzygj/s7653p/202003/46c9294a7dfe4cef80dc7f5912eb1989/files/ce3e6945832a438eaae415350a8ce964.pdf), the recommended antiviral drugs are lopinavir/ritonavir, chloroquine phosphate and other drugs.

The Chinese have decreased the current epidemic situation in China by using the recommended drugs. The relief of the epidemic in most provinces of China has at least confirmed the effectiveness of the treatment to a certain extent, but further strong and effective, evidence-based data is needed.

The trial will be conducted in a clinical outpatient and inpatient setting by experienced clinicians, and participants will be recruited from the patient base of the other three hospitals participating in the trial. The purpose of this prospective, open-label, multicenter randomized controlled, comprehensive clinical study is to evaluate the efficacy and safety of chloroquine phosphate and lopinavir/ritonavir in patients with mild/general COVID-19 infection. The results of this study should provide meaningful information and evidence for clinical practice and should help to design a proven and reasonable RCT soon.

### Limitations

Randomized controlled studies still have some design limitations. First, the sample size we use is relatively small and the 28-day treatment period is short. Therefore, we will not be able to estimate possible relapses of pneumonia after long-term treatment. Second, the pathophysiology of novel coronavirus pneumonia has not been elucidated. As only clinician assessment is used (including lung computed tomography (CT) results and count of viral load), there is no objective indicator to judge the effect of treatment on COVID-19 infection. Finally, the follow-up period in this study was relatively short. In light of these limitations, we will develop a more reasonable treatment cycle and follow-up period to explore the efficacy of chloroquine in patients with COVID-19.

We also know that there will be many biases in the open trial, and we have taken a number of measures to control the possible bias in the trial, as follows:

(1) Strict exclusion criteria are formulated to effectively control other confounding factors that may affect the efficacy; (2) the trial uses random grouping to ensure that the two groups of patients are comparable; (3) before the patient signs the informed consent form, the researchers and the patients make full communication to ensure that the patients understand the entire trial content, and try to eliminate the impact of the patient’s psychological state on the trial effect; (4) the main and secondary indicators for evaluating the efficacy are objective indicators to avoid the influence of subjective factors; (5) before the start of the trial, the researchers will conduct unified system training to ensure the uniformity and correctness of data collection and index evaluation.

## Trial status

The trial was registered under the registration number ChiCTR2000029741(http://www.chictr.org.cn/showproj.aspx?proj=49263) on 11 February 2020. On 10 February 2020, this study was approved by the Medical Ethics Committee of the Fifth Affiliated Hospital of Sun Yat-sen University in Zhuhai, ZDWY[2020] Lunzi No. (K15–1). Unique Protocol ID: ZDWY.GRBK.011. Protocol version date: 7 February 2020. The first participant was randomized in February 2020, and recruitment is ongoing. It is estimated that the recruitment will be completed on 31 May 2020. The final results will be reported next year.

## Data Availability

The datasets used or analyzed in the current study are available from the corresponding author on reasonable request.

## Abbreviations

ACE2: Angiotensin-converting enzyme 2
AE: Adverse event
COVID-19: Corona Virus Disease-2019
CI: Confidence interval
CRF: Clinical research flowchart
CTCAE: Common Terminology Criteria for Adverse Events
HCoVs: Human corona viruses
HIV: Human immunodeficiency virus
ITT: Intention-to-treat
MAPK: Mitogen-activated protein kinase
PP: Per-protocol
RT-PCR: Reverse transcription polymerase chain reaction
S protein: Spike protein
SAE: Severe adverse event
SARS-CoV: Severe Acute Respiratory Syndrome Corona Virus
